## Abstract

**Background:**

Anterior cruciate ligament (ACL) injuries in female athletes lead to a variety of short- and long-term physical, financial, and psychosocial ramifications. While dedicated injury prevention training programs have shown promise, ACL injury rates remain high as implementation has not become widespread. Conventional prevention programs use a combination of resistance, plyometric, balance and agility training to improve high-risk biomechanics and reduce the risk of injury. While many of these programs focus on reducing knee abduction load and posture during dynamic activity, targeting hip extensor strength and utilization may be more efficacious, as it is theorized to be an underlying mechanism of injury in adolescent female athletes. Biofeedback training may complement traditional preventive training, but has not been widely studied in connection with ACL injuries. We hypothesize that biofeedback may be needed to maximize the effectiveness of neuromuscular prophylactic interventions, and that hip-focused biofeedback will improve lower extremity biomechanics to a larger extent than knee-focused biofeedback during dynamic sport-specific tasks and long-term movement strategies.

**Methods:**

This is an assessor-blind, randomized control trial of 150 adolescent competitive female (9–19 years) soccer players. Each participant receives 3x/week neuromuscular preventive training and 1x/week biofeedback, the mode depending on their randomization to one of 3 biofeedback groups (hip-focused, knee-focused, sham). The primary aim is to assess the impact of biofeedback training on knee abduction moments (the primary biomechanical predictor of future ACL injury) during double-leg landings, single-leg landings, and unplanned cutting. Testing will occur immediately before the training intervention, immediately after the training intervention, and 6 months after the training intervention to assess the long-term retention of modified biomechanics. Secondary aims will assess performance changes, including hip and core strength, power, and agility, and the extent to which maturation effects biofeedback efficacy.

**Discussion:**

The results of the Real-time Optimized Biofeedback Utilizing Sport Techniques (ROBUST) trial will help complement current preventive training and may lead to clinician-friendly methods of biofeedback to incorporate into widespread training practices.

**Trial registration:**

Date of publication in ClinicalTrials.gov: 20/04/2016. ClinicalTrials.gov Identifier: NCT02754700.

## Background

Injuries in female athletes are a major short and long-term individual and public health problem within the United States. The combination of a greater susceptibility to injury than male athletes and a 10-fold increase in the female sports population since the inception of Title IX has resulted in a dramatic increase in the incidence of anterior cruciate ligament (ACL) injuries in females [1]. In the United States, 100,000–250,000 ACL injuries occur each year [2, 3]. The costs exceed $650 million annually in female varsity athletics alone [4]. In addition, there is a strong association between ACL injury and the development of posttraumatic knee osteoarthritis at a relatively young age, which also occurs with much greater incidence in females than males [5, 6]. Thus, the long-term ramifications of such injuries are quite significant. Poor athlete compliance and the absence of widespread implementation of effective ACL injury prevention programs has resulted in a consistently higher risk of ACL injury in females despite considerable research in the field.

ACL injury prevention programs use various neuromuscular training modalities to modify the high-risk biomechanics associated with injury [7]. Past research indicates that high knee abduction moments (KAM) may be the most important movement strategy to target. Hewett et al. [8] prospectively evaluated adolescent female athletes prior to their athletic season and reported KAM to be the single best predictor of subsequent ACL injury. KAM has also been reported to be significantly higher in females compared to males during a variety of landing and pivoting movements [9–14]. Furthermore, females show significant increases in KAM following rapid growth during adolescence compared to males [13]. As such, sex differences in KAM may partly explain the drastic differences in injury rates between post-pubertal males and females. Additionally, lower extremity valgus alignments are often demonstrated by females at the time of injury [15–17]. There is relative consensus in the literature that approximately 70%–80% of ACL injuries are non-contact in nature [17–19]. Video analysis techniques have confirmed that most non-contact ACL injuries occur during a sharp deceleration or landing maneuver with the knee close to extension at initial ground contact [17]. Olsen et al. performed a videographic examination of ACL injury mechanisms in team handball and reported that the ACL injury mechanism in women was a forceful valgus collapse with the knee close to full extension, combined with tibial rotation [15]. These analyses demonstrate relatively common mechanisms, including valgus, extended knee and widened stance [18].

While these previous investigations provide an important understanding of the potential mechanics related to injury, it may be more relevant to define the inciting mechanisms that underlie the high injury risk mechanics to provide the potential to target modifiable contributors to injury. Imbalances in hip function may be potential factors related to lower extremity and ACL injuries in female athletes [20, 21], considering that males utilize 18% greater hip extensor moments during the concentric phase of landing compared to females [22]. Additionally, sex differences are present in hip joint posture at initial contact (greater flexion in males), peak internal hip extensor moment (greater magnitude in males) and a significant preference to underutilize the hip compared to the knee extensors [23], indicating that males utilize a different hip strategy during landing compared to females. The hip extensors (gluteus maximus, hamstrings) are not only important in extending from a squat position but also in eccentrically establishing or maintaining posture and balance when landing from a jump. The targeting of proximal mechanisms, notably the activation and strength of the hip extensors, may result in improved control of knee abduction load and posture, ultimately leading to a greater reduction in the risk of ACL injury in young female athletes [24].

Prophylactic neuromuscular training has been shown to increase active knee stabilization in the laboratory and decrease the incidence of ACL injury on the field and court of play in athletic female populations [2, 25–28]. Neuromuscular training facilitates neuromuscular adaptations that focus on joint stabilization and safe movement patterns. This training allows female athletes to adopt muscular recruitment strategies that decrease joint motion and protect the ACL from high impulse loading [26, 29]. However, inconsistent implementation [7], combined with low athlete compliance [30] has resulted in a lack of wide-spread reduction in ACL incidence [1] and an alarming increase in ACL reconstruction surgeries in females and patients younger than 20 [31].

Despite the lack of wide-spread reduction in ACL injuries, numerous components of neuromuscular training have proven beneficial in modifying high-risk biomechanics and decreasing injury risk. Technique feedback has been reported to be beneficial for athletes to improve biomechanics and has become a recommended component of ACL injury prevention practices [32]. Conventional ACL injury prevention programs utilize verbal feedback from clinicians, coaches, and/or teammates to correct mechanics such as the position of the athlete’s knees. However, the type of cuing may be very important, as instructional strategies emphasizing an external-focus may be more beneficial for retention and the transfer of learned biomechanics to sport activities than internally-focused cues [33]. More specifically, biofeedback has been successful in retraining the biomechanics of runners [34], but has yet to be incorporated in ACL injury prevention programs, despite a pilot study reporting that kinetic biofeedback given during squats rapidly transfers to dynamic drop landings [35]. Thus, further trials studying the methodology, implementation and efficacy of biofeedback as a complement to traditional neuromuscular based prevention programs is warranted.

This paper describes the design of the Real-time Optimized Biofeedback Utilizing Sport Techniques (ROBUST) trial, the first study attempting to describe the immediate effects and retention of specific neuromuscular movement training using biomechanical biofeedback in order to reduce the risk of ACL injuries in adolescent female athletes. The trial is designed to assess the effectiveness of biofeedback as a complement to traditional neuromuscular prophylactic training and to identify whether feedback targeting the risk of injury (knee abduction load) or an underlying mechanism of injury (underutilization of the hip musculature) is more beneficial in this athletic population. Given the relatively high-risk of injury in female athletes, the grueling process of surgery and rehabilitation, and the impending early development of osteoarthritis, this trial has the potential to positively impact current preventive strategies. This manuscript will further explain in detail the injury prevention training program, biofeedback methodology, and screening of biomechanical outcome variables of this randomized control trial.

### Hypotheses

Our central hypothesis is that biofeedback methodology will maximize the effectiveness of neuromuscular prophylactic interventions. More specifically, we hypothesize that ROBUST training (both knee- and hip-focused) will lead to significantly reduced knee abduction load during double-leg jump landings, but that hip-focused ROBUST training will significantly reduce knee abduction load during a high-risk unplanned cutting task compared to knee-focused training. Further, we hypothesize that participants that receive hip-focused ROBUST training will best retain improvements in knee abduction load six months following training.

## Methods/design

### Study design

ROBUST is a prospective, randomized, active comparator, open blinded, end-point trial. Participants will be randomized into one of three study arms 1) hip-focused biofeedback, 2) knee-focused biofeedback, and 3) sham biofeedback. Each participant will provide written participant consent, and/or parental consent and participant assent as appropriate. All participants will be tested immediately before (pre-test), immediately after (post-test), and 6 months after (retention) a 6-week prophylactic neuromuscular training program. The training program will be performed 3 times a week, with augmented biofeedback (according to group designation) 1 time a week. All testing and training will occur at the High Point University Human Biomechanics and Physiology Laboratory. Figure 1 provides a flowchart of the design of ROBUST. Researchers responsible for collecting the primary outcome measures will be blinded to the participant’s group designation. While participants randomized to the study arms of the trial will not be blinded, we will also make every effort to maintain the blinding of the researchers responsible for delivering the interventions. In addition, the investigators and biostatistician will remain blinded to the group status during data management and analysis. In case a participant needs to be treated for an injury during the study period, the treating clinicians will not be aware of the group assignment. In addition, teams consisting of a trainer and blinded research assistants will be maintained as separate, functioning teams throughout the study to minimize the chances of unblinding. The study protocol was approved by the Institutional Review Board at High Point University. Additional information can be found at: Clinicaltrials.gov (Identifier: NCT02754700).

**Fig. 1 Fig1:**
[figure not shown]
Flow diagram of study participants randomized into three arms of ROBUST trial: ROBUST (H): Hip-focused biofeedback, ROBUST (K): Knee-focused biofeedback, and CONTROL: Sham biofeedback

### Participants

One hundred fifty female soccer players between the ages of 9 and 19 will be recruited from local soccer clubs and high schools for this study. Recruitment will be performed primarily through discussions with club presidents, athletic directors, directors of coaching, coaches, and parents. The study sample will consist solely of female youth soccer players that participate on a competitive team at the time of enrollment. Participants will be excluded if they are not currently able to participate in sport due to an injury or cannot commit to participating in the 6-week intervention.

An equal sample size of *N* = 50 will be randomized to each of the three study arms. Assuming 20% of loss to follow up, a sample size of 40 is expected in each group at the conclusion of the study. Under this assumption, it was estimated that one-way analyses of variance will have 80% of power to detect at the 0.05 level a difference in means characterized by a variance of means of 0.082 (i.e. the averaged group mean deviations from the grand mean being 0.082 or higher of the common standard deviation). Previous results suggest an improvement in knee abduction load between two forms of biofeedback training with estimated mean+/-SD of 11+/-6 Nm vs. 2+/-10 Nm, indicating sufficient statistical power in this study [35].

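### The sample-size statement explains a variance of means of 0.082 as a deviation of 0.082 SD; the effect with 80% power is about 0.29 SD, some 3.5 times larger

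*Protocol article*

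**What the plan says.** The sample size is set in the Participants section under Methods/design. Fifty players are randomized to each of three arms, and "Assuming 20% of loss to follow up, a sample size of 40 is expected in each group". On that basis the article states that "one-way analyses of variance will have 80% of power" at the 0.05 level for "a difference in means characterized by a variance of means of 0.082". A bracket opening with i.e. then restates the same effect in words: "the averaged group mean deviations from the grand mean being 0.082 or higher of the common standard deviation". The next sentence cites an earlier biofeedback result, "estimated mean+/-SD of 11+/-6 Nm vs. 2+/-10 Nm", as a sign that power is sufficient.

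**The concern.** The sentence gives the detectable effect twice and presents the two versions as equal. A variance of means is an average of squared deviations, in units of the common variance. The bracket attaches the same number to unsquared deviations, in units of the common SD. The figure 0.082 cannot be both, so at most one version can go with 80% power at 40 per arm.

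The bracket is the version that a reader without statistical training will use, and the document states a minimum detectable effect nowhere else. Taken at face value, it says the trial can find arm means that typically lie 0.08 SD from the overall mean. A non-significant result, for instance in the hip-versus-knee comparison named under Hypotheses, could then be taken to exclude differences that the trial had little chance of seeing. Anyone who reuses the figure to plan a later trial would carry the error forward.

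**Working it through.** **Inputs, all from the Participants section.** Three arms; 40 evaluable per arm, so N = 120; alpha 0.05; stated power 80%; effect 0.082; 20% loss. The loss allowance is consistent: 40 / (1 − 0.20) = 50 per arm.

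**Formula.** One-way ANOVA power comes from the noncentral F distribution with k − 1 = 2 and N − k = 117 degrees of freedom and noncentrality λ = N·f². Here f² is the variance of the group means (divisor k) over the common within-group variance, so f is the root-mean-square deviation of the means in SD units.

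**Step 1: reproduce the plan's figure.** With f² = 0.082, λ = 120 × 0.082 = 9.84 and power is **79.8%**. This matches the stated 80% (the exact value for 80% is f² = 0.0824). Other readings of the number do not match:

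| Reading of 0.082 | Per arm | Power |
|---|---|---|
| Variance of means, divisor k | 40 | 79.8% |
| Variance of means, divisor k − 1 | 40 | 61.3% |
| Sum of squared deviations | 40 | 34.0% |
| Variance of means, divisor k | 50 | 88.5% |

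The calculation therefore used 0.082 as a variance of means with 40 per arm.

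**Step 2: take the bracket as written.** With f = 0.082, f² = 0.082² = 0.00672 and λ = 120 × 0.00672 = 0.807. Power is **11.4%** at 40 per arm and 13.2% at 50 per arm. Reaching 80% would take about 479 evaluable per arm.

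**Step 3: size of the discrepancy.** √0.082 = 0.286 SD, and 0.286 / 0.082 = 3.49.

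**Step 4: the same check with mean absolute deviation.** If the averaging in the bracket is of absolute deviations, the answer depends on the pattern of means.
- A variance of 0.082 implies a mean absolute deviation of 0.234 SD (evenly spaced arms) or 0.270 SD (one arm apart). These are 2.9 and 3.3 times 0.082.
- A mean absolute deviation of 0.082 SD gives power of 14.9% (evenly spaced) or 12.3% (one arm apart).

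**Step 5: the detectable effect as a difference between arms.**
- One arm differs by δ from two equal arms: the variance of means is 2δ²/9, so δ = √(0.082 × 9/2) = **0.61 SD**.
- Evenly spaced arms with range R: the variance of means is R²/6, so R = √(0.082 × 6) = **0.70 SD**.
- The bracket's 0.082, read as f, would imply 0.082 × 3/√2 = 0.17 SD and 0.082 × √6 = 0.20 SD.

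**Step 6: in Nm, under an assumption.** The article gives no group sizes for the earlier result. With equal weights, the pooled SD is √((6² + 10²)/2) = 8.25 Nm, and the two differences are about 5.0 and 5.8 Nm. Across SDs from 6 to 10 Nm they run from 3.6 to 6.1 Nm and from 4.2 to 7.0 Nm.

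**Step 7: the cited earlier result.** (11 − 2) / 8.25 = 1.09 SD. With the third arm's mean anywhere from the midpoint to one end, the variance of means is 0.20 to 0.26. This is well above 0.082, and power at 40 per arm exceeds 99%.

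**The case against.** The strongest reply is that the operative specification is right. The test, alpha, power, evaluable number and variance of means agree with one another, and only an explanatory bracket is wrong, perhaps because the word squared was dropped. Neither the Randomization section nor the Data and statistical analysis section depends on it. The next sentence shows that the authors had a gap of 9 Nm in mind, about 1.1 SD, which the planned size covers easily. The document also nowhere proposes to read a null result as excluding small effects.

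Most of this stands, and it limits the finding: the trial does not have 11% power for its intended effect, and nothing here shows it to be underpowered. Two cautions on precision are also fair. The figures of 3.5 times and 11.4% belong to the root-mean-square reading; with absolute deviations they become 2.9 to 3.3 times and 12% to 15%. The Nm figures rest on an equal-weight pooled SD.

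None of it rescues the bracket. Its unit is explicitly the common SD, no reading of the averaging brings 0.082 SD near 80% power, and no other text corrects it. The anticipated effect in the next sentence is not a minimum detectable effect, so it does not replace the wrong one.

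**Conclusion.** The concern holds. The 80% power claim is correct for a variance of means of 0.082, and the explanation of that number is wrong. The typical deviation of the arm means at which the trial has 80% power is 0.286 SD, not 0.082 SD: 3.5 times larger as a root-mean-square, and about 3 times larger as a mean absolute deviation. For the effect as the bracket words it, power would be 11.4% (12% to 15% with absolute deviations).

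These figures assume the omnibus one-way ANOVA the article names, a common within-arm SD, 40 evaluable per arm and alpha 0.05. The error lies in the stated sensitivity of the trial, not in its size.

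**What to change.** Keep the sample size, the 80% figure and the variance of means. Replace the bracket with:

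> i.e. a root-mean-square deviation of the group means from the grand mean of 0.286 common SD (Cohen's f = 0.286), equivalent to one arm differing from the other two by 0.61 SD, or to a 0.70 SD spread between evenly spaced arms

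If values in Nm are added, state the SD used and that 8.25 Nm assumes equal weights for the two earlier groups.

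The cost is one sentence. The stated detectable effect becomes less favourable; recruitment, randomization and analysis are unaffected. The trial report should use the corrected figure when it interprets non-significant comparisons.

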### Randomization

Enrolled subjects will be randomized to a biofeedback group using computer-generated blocks after completing pre-test screening. A clinical coordinator, independent of the study statistician and research assistants conducting the analyses, trainer, and evaluator, will generate a random sequence of numbers which will be stored in a spreadsheet accessible to only non-blinded study staff. Participants will be assigned to the study arms in the randomization scheme according to the order that their baseline visit was completed. The clinical coordinator will generically label the treatment assignments to group A, B, and C to ensure blinding is maintained for researchers responsible for pre- and post- testing, and for researchers responsible for providing the prophylactic intervention. Only the clinical coordinator and researchers responsible for providing ROBUST training will be privy to the participants’ group designation.

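### Allocation concealment is not assured: the pre-generated list is open to unblinded staff, apparently including the biofeedback trainers, and fixed arm letters add a separate blinding risk

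*Protocol article*

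**What the plan says.** Under Randomization, the protocol article gives these facts:

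- **Timing and method.** "Enrolled subjects will be randomized to a biofeedback group using computer-generated blocks after completing pre-test screening". No block size is given.
- **Who makes the list.** "A clinical coordinator, independent of the study statistician and research assistants conducting the analyses, trainer, and evaluator", produces it.
- **Where it is kept.** The product is "a random sequence of numbers which will be stored in a spreadsheet accessible to only non-blinded study staff".
- **How entries are used.** "Participants will be assigned to the study arms in the randomization scheme according to the order that their baseline visit was completed".
- **Who knows the arm.** "Only the clinical coordinator and researchers responsible for providing ROBUST training will be privy to the participants’ group designation".
- **Labels.** A further task of the same person is this: "generically label the treatment assignments to group A, B, and C to ensure blinding is maintained for researchers responsible for pre- and post- testing". The same sentence extends this protection to the staff giving the prevention training.

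Under Study design, outcome collectors, investigators and the biostatistician are to be blinded, participants are not, and trainers and research assistants work in separate teams. The same section adds that "we will also make every effort to maintain the blinding of the researchers responsible for delivering the interventions", without saying which interventions are meant.

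**The concern.** Two issues need to be kept apart.

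The first is allocation concealment. Whoever decides if and when a player enters the trial should not know which arm comes next. The article sets access to the list by blinding status, which is a different criterion. Someone who must know the arm of participants already assigned does not need to see assignments still to come. If a person who can read ahead also has a say in eligibility or in the order of baseline visits, selection bias can enter. Two points leave room for discretion: the exclusion under Participants of players who cannot commit to the six-week programme, and the timing of visits.

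The second is blinding after assignment. One fixed letter per arm ties all members of that arm together. Participants know what was on their screen, and all testing and training take place in one laboratory. If staff who see the letters learn what one letter stands for, they learn it for everyone in that arm. Testers have some influence on results. They rule on repeated trials, give verbal encouragement in strength testing and judge posture in the plank test. Under Retention testing, the same researchers return at six months, so a decoded letter would carry forward.

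**Working it through.** **Plan figures used.** The article plans 50 per arm in three arms, which gives 3 × 50 = 150. With 20% loss, 50 × (1 − 0.20) = 40 per arm, as stated. The stated 80% power also reproduces: λ = 120 × 0.082 = 9.84 with 2 and 117 degrees of freedom gives 0.798. This point does not depend on the power figure and changes no design figure.

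**Who can read ahead.**

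1. The list exists before participants are assigned and sits in a file that only unblinded staff can open.
2. The staff named as knowing group membership are the coordinator and the biofeedback providers. The natural reading is that these are the unblinded staff.
3. Entries are used in order of completed baseline visit, so the next entry belongs to the next player to finish the pre-test.
4. No step is described that hides later rows from those who can open the file.
5. The Participants section names recruitment channels. It does not say which staff enrol, judge eligibility or schedule visits, so list-holders are neither given these tasks nor kept from them.

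**How predictable the next arm is.**

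- No information, three equal arms: 1/3 = 0.33.
- Sight of the list: 1.00.
- List hidden, but past assignments and block size known, always guessing the arm with most places left. Block size is my assumption, because the article gives none:
  - Block of 3: (1/3 + 1/2 + 1)/3 = 0.61.
  - Block of 6: (1/3 + 2/5 + 1/2 + 8/15 + 3/5 + 1)/6 = 0.56.
  - Block of 9, by the same method: 0.53.

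Hiding the list therefore moves a biofeedback provider from certainty to at most about 0.61 under these block sizes. It does not by itself bring the figure down to 0.33.

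**Reach of a decoded letter.** Among people who see each participant's letter, one decoded letter reveals up to 150/3 = 50 participants (33%), and two reveal all 150. These are ceilings. Pre-tests come before randomization and cannot be affected, and tests done before a leak are untouched. If testers never see the letters, a remark about the screen unblinds only the participant who made it.

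**Study design against Randomization.** One section promises every effort to blind those who deliver the interventions. The other makes the biofeedback providers aware of the arm, as they must be in order to run the arm-specific display and instructions described under ROBUST. Both can be true only if the first sentence means the prevention trainers alone, and it does not say so.

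**The case against.** The case on the other side is substantial.

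- **Concealment concerns those who control entry.** No section gives biofeedback staff a role in enrolment, eligibility or scheduling. Players are enrolled and pre-tested before assignment, the list-maker is independent of trainer and evaluator, and strict visit order limits discretion. This stands. A reader might infer that allocation is simply not concealed. The text does not support that, because concealment fails only if a list-holder can also influence entry or visit order, and the article does not say so.
- **The access wording is an outer limit.** It does not say that every unblinded person opens the whole list, and knowing group membership may mean only the arm of participants already assigned. This also stands. Advance sight by the biofeedback providers is the natural reading of two sentences together, not an explicit statement.
- **The letters are not the only shield.** Separate teams are planned, and the article does not say that testers hold each participant's letter. A reader might infer that a single leak would unmask a whole arm. That holds only for people who see the labels.
- **The primary outcome limits the harm.** Knee abduction moment comes from motion capture and force plates, and landing and cutting trials are repeated on written criteria. This reduces the scope for tester influence on the primary outcome. Encouragement and posture judgement matter more for the secondary strength and core tests.
- **A journal article condenses the full protocol.** Release procedures and file permissions may be set out elsewhere. That would answer a complaint about missing detail. It does not answer the access rule that the article does state, which is drawn by blinding status, or the mismatch between the two sections.

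**Conclusion.** The point holds in a conditional form and is worth acting on. It does not invalidate the trial.

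- **Concealment is not assured.** Upcoming assignments are open to the coordinator and, on the natural reading, to the biofeedback providers, with no stated separation from enrolment or scheduling. Someone with the list predicts the next arm with probability 1.00 rather than 0.33. Whether that knowledge could affect who enters, or when, depends on roles that the article does not describe.
- **The letters are a separate blinding risk.** Up to 50 participants per decoded letter could be revealed, on the assumption that testers or prevention trainers see individual letters.
- **The mismatch on who is blinded is a plain wording fault.** It needs no assumption.

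The size of any bias in the results cannot be computed from the document.

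**What to change.** 1. Restrict the sequence to the coordinator. Release one assignment at a time, only once that participant's pre-test is complete and recorded. Biofeedback staff then see only the arm of participants already assigned.
2. Give testers and prevention trainers no group letter, since they need none for their work. Use A, B and C only in the analysis data set.
3. Correct the Study design section to say that testers and prevention trainers are blinded and that ROBUST biofeedback providers are not.

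The cost is minor administrative set-up, either file permissions or an electronic randomization module. The article mentions REDCap only for a survey, so it should not be assumed that such a module is already in place. No participants are added and no design figure changes. Recruitment began in June 2016 according to the Timeline section, so items 1 and 2 can protect only assignments and tests still to come. For the rest, the trial report should state who had access to the list and to the letters.
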